### 1.2. Primary Aims

1. To test the comparative effectiveness of E-WORTH versus Streamlined HIV Testing on primary outcomes of decreasing biologically confirmed STIs and the number and proportion of unprotected sexual acts at the 12-month follow-up and secondary outcomes of reducing drug use, increasing utilization of drug treatment, linkage to HIV care and ART adherence (for HIV+ participants), decreasing partner violence and recidivism.
2. To test if the effectiveness of E-WORTH on study outcomes is moderated by client characteristics (e.g. client subgroups defined by socio-demographics and psychosocial characteristics)
3. To estimate the costs and comparative cost-effectiveness of E-WORTH versus Streamlined HIV Testing on STI infection rates, drug use and projected number of HIV cases averted at the 12-month follow-up.

4. To examine qualitatively and quantitatively how multi-level theory-driven factors may influence the fidelity of implementation and effectiveness of E-WORTH and Streamlined HIV testing on study outcomes.

1.3 Rationale: Despite extremely high rates of HIV and STIs that have been found among women on probation, parole or ATI programs nationwide, to date, WORTH is the only intervention that has been found to be efficacious in increasing condom use and reducing sexual risks among justice involved women in the U.S. Our recent study of 337 drug-involved women on probation or community supervision in NYC found that 17% of the 221 Black women tested positive for HIV and 30% tested positive for an STI . The HIV rate found among Black women on probation indicates a highly concentrated epidemic, comparable to rates in sub-Saharan Africa; however, no HIV prevention or testing services are provided in NYC probation sites. The proposed study will address this critical gap in services for Black women drug users in probation settings by testing the effectiveness and cost-effectiveness of the 5-session multimedia E-WORTH intervention.

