**2.3 Power Analyses:** From ICC estimates based on the previous WORTH trial, variance inflation factors were calculated to generate effective sample sizes used in G\*Power for Aim 1. For cumulative STI incidence, we assumed a 50% reduction (on a background cumulative incidence of 20.5%) to be clinically meaningful to detect via Poisson regression; for behavioral outcomes, projected means, standard deviations, allow for effect size  $f^2$  to be calculated and used in G\*Power. Results for primary outcomes (Figure 3) indicate that 80% power is achieved for the rate-limiting outcome (i.e., cumulative STI incidence) with an effective sample size of 372 participants; translating to a sample size of 378 participants after accounting for ICC. We then increased the starting sample size to 420 to safeguard against attrition (modeled as a complete loss of 10% of data as conservative estimate since the efficacy trial of WORTH achieved a 91% retention rate at 12-month follow-up and many of those cases provided data at earlier assessment points, thus were not “fully” missing). For secondary outcomes, power analyses participants/arm indicate 80% power to detect differences for effect sizes  $f^2 = .03$  to  $.04$  (for  $\alpha = .1$  TO  $.5$ ) with sample sizes as low as 369.

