### 3.5. Randomization

Consistent with an intention-to-treat approach for data analyses, participants will only be considered enrolled in the trial when they have been randomly assigned to a study arm. We will implement urn randomization to “force” a balance (without adding bias) between study arms with respect to the number of women per arm so that half of the women will be randomized to E-WORTH and immediately receive the individual Streamlined HIV test session followed by 4 E-WORTH group sessions and half will be randomized to and immediately receive the Streamlined HIV Testing session alone. The randomization program, which has been adapted from our previous RCTs, will also feature a combination of randomization and assignments to balance the number of women per condition per site so that the number of women assigned to each condition will be distributed across probation, parole or designated ATI program and study sites. In addition, participants randomized to the intervention arm will complete the intervention individually if less than 4 participants are enrolled at a given site in 28 calendar days. Additionally, the assignment window during the Treatment as Usual condition assignment phase will open after the first participant is assigned. We will explain the randomization process to participants during informed consent. The randomization and assignment protocol will also

ensure moderators of intervention effects assigned to study arms, thus minimizing the possible introduction of bias that can occur with urn randomization or block permutation techniques.

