At each interim time point as well as after study completion, analyses will follow the data analysis plans for primary aims described in the original proposal. Interim analyses will focus on the study's primary aims. If at any of the interim analyses the statistical significance for all biological outcomes related to primary aims (i.e., cumulative STI incidence), exceeds the a priori  $\alpha < .05$  criterion at that time point, the study will be stopped since the inference will be that significant benefit of assignment to one study arm over the other will have already been demonstrated. We note that this represents two-sided hypothesis testing since demonstrating benefit with respect to disease prevention of one intervention over the other (regardless of the content of that intervention) is of public health value and importance. With respect to futility, stopping rules are concerned with effect size estimates indicating a null result is inevitable given the planned total sample size. Stopping a study in such circumstances avoids additional expenditure of time, fiscal, and human resources that would nevertheless ultimately result in lack of evidence of superiority of one intervention over the other. At each interim analysis time point, a post hoc power analyses will be conducted to determine the minimum sample size needed to achieve 80% power to reject the null hypothesis given point estimates and standard errors of efficacy estimates using data collected to date. If the estimated minimum sample size for power analyses using  $\alpha =$

.05 exceeds the planned enrollment of N=420 women for all of the biological and self-reported behavioral outcomes associated with the primary aims, the investigative team will notify the NIDA Program Official (PO) of such findings. Based on the magnitude of the difference between the estimated minimum sample sizes needed for 80% power and targeted sample size, in addition to recruitment rates to date, the investigative time and NIDA PO will discuss and agree whether the study should be stopped due to reasons of futility or whether modifications to the study design/protocols (e.g., increasing planned enrollment, hiring of additional recruitment staff, etc.) can be implemented to avoid futility.

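### Section 2.3 states 80% power for secondary outcomes without exempting linkage to HIV care and ART adherence, which can be measured only in about 64 to 71 HIV-positive women and have power well below 80%

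*Supplement*

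**What the plan says.** Section 1.2 (Primary Aims) lists the secondary outcomes of Aim 1. Among them are "linkage to HIV care and ART adherence (for HIV+ participants"). Section 1.3 reports that in the team's earlier study "17% of the 221 Black women tested positive for HIV".

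Section 2.3 (Power Analyses) covers secondary outcomes in a single sentence: "For secondary outcomes, power analyses participants/arm indicate 80% power to detect differences for effect sizes" of f² = .03 to .04, "with sample sizes as low as 369". It names no exception. The same section plans 420 women, with 10% complete loss leaving 378. Section 2.2 says that secondary outcomes will be analysed much as the primary ones are.

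HIV infection is not an inclusion criterion (section 6), and nothing in the plan enriches the sample for it. The Data Analyses Plan at the end of the protocol gives models for repeated outcomes but no sample size and no mention of an HIV-positive subset.

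**The concern.** An outcome that can be observed in roughly one woman in six cannot have 369 analysable women in a trial of 420. As printed, the 80% statement nevertheless covers every secondary outcome. If it stands, a non-significant result on linkage or ART adherence could be presented as coming from an adequately powered comparison, when only a much larger effect than the one stated was likely to be detected. The primary outcomes and the interim rules do not depend on these two outcomes.

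**Working it through.** **Inputs.** f² = .03 and .04, N = 369, 420 enrolled and 378 retained (section 2.3). HIV prevalence 17% of 221 (section 1.3). Equal allocation: "half of the women will be randomized to E-WORTH" (section 3.5, Randomization). Alpha .05, two-sided: section 13 gives both for the primary aims ("We note that this represents two-sided hypothesis testing"), and I assume the same here because section 2.3 gives no separate level. The supplement holds two copies of the power sentence. One prints α = .1 to .5 and the other r = .1 to .5, so I read that range as a correlation. I read 369 as a total, since 369 per arm would be 738 and exceed 420.

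**Formula.** Regression F test of the G*Power type: noncentrality λ = f² × N, with u and N − u − 1 degrees of freedom. The documents do not state u.

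**Step 1: the plan's own figure.** With f² = .03 and u = 3, the smallest N for 80% power is 368, and power at 369 is 80.2%. So 369 reproduces. At f² = .03, u = 1, 2 and 4 give N = 264, 325 and 403. The match holds at one end of the stated range only: with u = 3 and f² = .04, power at 369 is 91%. With u = 1, power at 369 is 91% (f² = .03) and 97% (f² = .04).

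**Step 2: women who can contribute.**
- .17 × 420 = 71.4, about 71.
- .17 × 378 = 64.3, about 64.
- 17% of 221 is about 38 women, with a 95% Wilson interval of about 13% to 23%. Near its ends, .125 × 378 is about 47 and .225 × 420 is about 94.

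**Step 3: power with one observation per woman.**

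| HIV-positive N | u = 3, f² .03 / .04 | u = 1, f² .03 / .04 |
|---|---|---|
| 47 | 14% / 17% | 21% / 27% |
| 64 | 18% / 22% | 28% / 35% |
| 71 | 19% / 25% | 30% / 38% |
| 94 | 25% / 33% | 38% / 48% |

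**Step 4: detectable effect at 80% power, one observation per woman.** At N = 71 and 64, f² is .114 and .127 with u = 1, or .163 and .182 with u = 3. These are about 3 to 6 times the stated .03 to .04 (.114/.04 = 2.9; .182/.03 = 6.1). Conversely, the most favourable single-observation case (u = 1, f² = .04) needs 199 women, which is 47% of 420 or 53% of 378.

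**Step 5: pooling three follow-ups.** If f² is per time point, the effective N is 3N / (1 + 2r), with r assumed exchangeable. At r = .1 this is 2.5N (160 and 177.5 for 64 and 71). At r = .5 it is 1.5N (96 and 106.5). Over f² = .03 to .04, power is about 25–59% with u = 3 and about 39–75% with u = 1.

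One combination passes 80%: 94 women, u = 1, f² = .04 and r = .1 give 86%. That needs the top of the prevalence range, full retention, the larger effect and the lowest correlation together.

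**The case against.** The strongest reply is that the sentence in section 2.3 is visibly garbled and, as printed, conditional: it gives 80% power at samples as low as 369 and does not promise 369 women for every outcome. On that view this is an omission and not a false calculation. That stands in part. The 369 reproduces, and a reader who infers that the calculation itself is wrong would go beyond the documents. But no exception is stated anywhere, and section 1.2 puts these two outcomes in the same list as the rest.

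The second reply is that no single power figure is firm. The numerator df is inferred. The 64–71 is a projection from an earlier sample. The Data Analyses Plan models behavioural outcomes over the whole follow-up, so repeated measures may add information. All of that stands, and it is why 18–38% should not be read as the trial's actual power for these outcomes: it is the range for one observation per woman. Against this, section 2.2 words the Aim 1 hypotheses at 12 months, and the stated f² may already include any gain from repetition. The documents do not settle either point, and pooling does not reach 80% at 64–71 women.

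Third, the HIV-positive qualifier could attach to ART adherence alone. Linkage to HIV care still presupposes infection. The linkage procedure in section 3.5 (Biological Assays) is directed at women who newly test positive, and HIV testing may be declined, so the number for linkage may be smaller still.

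**Conclusion.** The point holds as an unstated exception in the power section. For linkage to HIV care and ART adherence, power at the stated effect is well below the 80% given for secondary outcomes: about 18–25% (3 df) or 28–38% (1 df) with one observation per woman, and about 25–75% if three follow-ups are pooled. This rests on 17% prevalence, two-sided alpha .05, an inferred df and, for pooling, an assumed correlation of .1 to .5. The direction is secure at the expected 64–71 women; the exact figure is not.

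A reader might infer that the trial is too small, or that these outcomes must be dropped or confined to description. The documents do not support that. The primary STI sample size is unaffected, and low power in two secondary outcomes is acceptable once it is stated.

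**What to change.** In section 2.3:
- Limit the 80% statement to secondary outcomes measured in all women.
- For ART adherence, state the expected number (about 64–71 at 17%, about 47–94 over the uncertainty in that estimate). For linkage, say whether it covers all HIV-positive women or only the newly diagnosed, and give the matching number.
- Give the power or detectable effect for both, with the test df, the prevalence, and whether repeated measures are pooled and at what correlation. If the detectable effect is expressed as a difference in percentages, label the control-arm rate as an assumption and show a range, since the documents give none.
- State, there and in the Data Analyses Plan, that a non-significant result on either outcome will be reported with its confidence interval and not read as evidence of no effect.

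The cost is wording only: no extra participants, visits or analyses.

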### 3. Study Procedures

#### 3.1. The Study Team

This research will be undertaken by the Social Intervention Group (SIG) at the Columbia University School of Social Work. SIG is a multidisciplinary research center with a strong infrastructure and experienced researchers and staff. This study benefits from SIG's extensive

clinical trials experience, an investigative team with longstanding collaborative relationships, and the availability of established and tested protocols from previous randomized controlled trials conducted in community correction sites. The investigative team successfully completed an efficacy trial of Multimedia E-WORTH intervention with drug-involved women under community supervision with the New York City Department of Probation. The investigative team will replicate many of the approaches, procedures, and protocols that achieved success during the pilot trial, which also did not have any adverse events. The study research team will include a project director, a data manager, a clinical supervisor who is a graduate research assistant and 2 research assistants who will be responsible for recruitment, administering assessments and retention of participants. For this study, we will have a service agreement contract with Fortune Society who will hire 6 providers (or 1 full-time equivalent) to conduct the interventions for both study arms. They will not be involved in obtaining informed consent or collecting any data for the study from participants. Fortune Society has multiple longstanding service contracts with the New York City Department of Probation. We will recruit participants from probation, parole or designated ATI program sites located throughout in New York City. We have successfully collaborated with the New York City Department on three randomized controlled trials since 2009. Potential participants in ATI programs or parole will NOT include individuals who are detained in a residential facility or treatment center as a form of sentencing or alternative to incarceration.

### 3.2. Overview of Study Participation

This randomized controlled trial will be conducted with 420 drug-involved Black women from probation, parole or designated ATI program sites located throughout communities in NYC heavily affected by HIV and STIs. Eligible women will be randomly assigned to: (1) E-WORTH consisting of an individual evidence-based Streamlined HIV Testing session followed by a 4-session group-based multimedia HIV intervention (E-WORTH) or (2) an individual Streamlined HIV Testing session alone (Streamlined HIV Testing), which will serve as the comparison condition. Both conditions will be delivered at two Fortune Society Sites (located in Harlem and in Long Island City). If participants live too far to attend sessions at these sites, Fortune staff may also deliver intervention sessions at our community research site or at a NYC DOP site approved by the appropriate DOP Assistant Commissioner. Repeated assessments will occur at baseline and 3, 6, and 12-months post intervention. For participants residing out of New York City during their follow up period, or are otherwise prevented from traveling to study sites to complete a follow up assessment, we will send a link to follow up assessments directly to the participant's e-mail on a password protected PDF document. We will conduct repeated assessments and qualitative in-depth interviews on multi-level factors that may influence the effectiveness of E-WORTH and Streamlined HIV Testing on study outcomes with Fortune providers delivering the interventions, frontline probation, parole or designated ATI program staff (e.g. probation officers), probation administrators and probation clients. Self-reported data on behavioral outcomes will be collected from participants via audio computer-assisted self-interview (ACASI). Primary outcomes will be measured via biological assay for infection by *Neisseria gonorrhea*, *trichomonas*, and *Chlamydia trachomatis*, the most common STIs found among women in NYC.

We will also conduct qualitative interviews with 20 E-WORTH participants who reported episodes of homelessness and depression when completing assessments at baseline, 3-, 6- and/or 12-month. The goal of these interviews is to better understand the relationship between

homelessness and depression among women involved in the criminal justice system who are also at risk for HIV and other STIs.

We will conduct focus group interviews with Eworth and Fortune society staff to better understand 1) study implementation and barrier; 2) Linkage to care, to **understand barriers and facilitators to better understand care and usages of housing, employment, mental health and sexual health services;** 2) **Sexual Health Literacy to access community sexual health literacy, what kind of information and where they are getting;** 3) **Opioid and Community to access opioid use in the community and attitudes towards Medication-Assisted Treatment (MAT) Medication-assisted treatment (MAT), including opioid treatment programs (OTPs), combines behavioral therapy and medications to treat substance use disorders.;** 4) **Linkage to care barriers to understand barriers and facilitators to better understand care and usages of housing, employment, mental health and sexual health services.**

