## Study Description

### 1. Study Purpose and Rationale

1.1 Purpose: The proposed study is a randomized controlled trial (RCT) that will rigorously evaluate the effectiveness and cost-effectiveness of delivering a multimedia evidence-based intervention (E-WORTH which is an acronym for Empowering African-American Women on the Road to Health) and streamlined HIV testing to prevent HIV and other sexually transmitted infections (STIs) with Black/African-American (hereafter referred to as Black) women drug users in probation, parole or alternative to incarceration programs (ATI hereafter) sites in New York City (NYC), compared to streamlined HIV testing alone. Repeated assessments will occur at baseline and 3, 6, and 12-months post intervention. The primary outcome will be to reduce cumulative incidence of biologically confirmed STIs (i.e., Chlamydia, gonorrhea and trichomonas. This study has the following specific aims:

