**WORTH Intervention Condition:** WORTH consists of one Streamlined HIV Testing session described below followed by four 1.5-hour group sessions of 3-8 women that will be delivered by a Fortune Society facilitator provider at the Fortune Society sites. The main multimedia components used in the WORTH: (1) Narrativity: Use of videos with fictional characters who resemble different life stories of Black women affected by HIV/AIDS, drug use and criminal justice. These characters provide inspirational messages, model group support and core risk reduction skills; (2) Skill acquisition using simulated video vignettes that provides instruction and demonstration of core skills (e.g., safer sex negotiation and problem-solving skills, technical condom use skills) using culturally congruent role models followed by simulated video vignettes of role play scenarios where participants are prompted to identify common pitfalls in using skills and to rehearse appropriate responses; (3) Individual interactive exercises and logs that are designed to enhance participant's recall of core knowledge and to provide a confidential space for participants to track their individual progress in reducing risky behaviors and achieving risk reduction goals, current and ideal future social networks, and the types of support for sustaining safer behaviors, and future plans; and (4) Facilitator interactive guide which acts as a road map, prompting the facilitator to move sequentially through each activity without the need to rely on notes or memory. The basic format of each E-WORTH session remains consistent following a sequence of 5 steps: (1) an opening (quote, song, poem) which will provide a brief culturally relevant point of inspiration to engage participants; (2) Check-in to review material from the previous session, (3) a discussion to raise awareness of links between IPV, drug use, criminal justice involvement and HIV risks; (4) a skills-building component relevant to the discussion; and (5) an individual computerized rating of their sexual and drug risks; (6) an individual computerized to set appropriate risk reduction goals and plan of action which they can text to themselves. (7) identification of service needs and appropriate referrals using a computerized service tool. E-WORTH more exclusively tailored to the realities of Black women on probation, parole or ATI programs, including: (1) adding recent HIV/STI statistics for Black women in NYC on probation, parole or an ATI program to raise awareness about the epidemic in their communities; (2) using only Black characters and narratives, incorporating Afro-centric messages that

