## 8. Informed Consent Process

8.1 Informed consent for participants for mainphase trial: If the participant still meets eligibility criteria, research staff will again describe the study, and the participant will be consented for participation in the study. The informed consent process will emphasize that involvement in research will include a baseline assessment, four intervention sessions, and three follow up assessments, for which the participant will be compensated. She will also be reassured that her decision not to participate or continue in the research study will not result in consequences from the court, NYC Department of Probation, Parole, ATI programs or the criminal justice system. If the participant agrees to take part in the study, she will sign the consent form and will be administered the baseline assessment and HIV/STI testing. After the baseline assessment and HIV/STI testing, the participant will be randomized into one of two conditions, and continue through the study as described in study procedures.

Research Assistants will go through the informed consent process with potential participants immediately prior to conducting the initial and the confirmatory screening interviews as well as

at the baseline and all follow-up CASI assessments. In addition, Research Assistants will administer the HIPAA consent form at the screening interview.

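### Follow-up is timed from the end of the intervention, which comes later in E-WORTH than in control by an unstated amount, so the 12-month STI comparison covers unequal time at risk and runs against E-WORTH

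*Supplement*

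**What the plan says.** **Visit timing.** Section 3.2 states: "Repeated assessments will occur at baseline and 3, 6, and 12-months post intervention". Sections 1.1, 2.1 and 3.4 use the same anchor. No section ties a follow-up visit to randomization.

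**Baseline swab.** Section 8.1: "After the baseline assessment and HIV/STI testing, the participant will be randomized into one of two conditions". The baseline swab therefore precedes assignment in both arms.

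**End of intervention, control.** Section 3.5 (Randomization) has control women "randomized to and immediately receive the Streamlined HIV Testing session alone". Their intervention ends with that one session.

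**End of intervention, E-WORTH.** The same section has E-WORTH women "immediately receive the individual Streamlined HIV test session followed by 4 E-WORTH group sessions". Section 3.6 describes the testing session as "followed by four 1.5-hour group sessions of 3-8 women". Neither section gives the interval between sessions or the length of the programme. Where groups do not fill, women will "complete the intervention individually if less than 4 participants are enrolled at a given site in 28 calendar days".

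**Meaning of the term.** Section 5 treats the post-intervention point as arm-specific. The evaluation form is given after the final session in E-WORTH and after the testing session in control.

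**Outcome and model.** Section 1.1: "The primary outcome will be to reduce cumulative incidence of biologically confirmed STIs". The Data Analyses Plan tests new STI at the 12-month follow-up by logistic regression and mentions no exposure time. The compensation list in Section 3.7 attaches a follow-up STI test to the 12-month visit only; a retesting payment is also listed, without a date.

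**The concern.** The outcome is infection acquired since a baseline that precedes randomization, but the closing date is set by an event after randomization that differs by arm. Followed literally, the plan swabs an E-WORTH woman later after her baseline than a control woman. The extra time at risk falls in one arm only, and a logistic model without a time term reads it as a difference in risk.

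The same wording weakens the intention-to-treat analysis. The visit date depends on when a woman attends her last session, and for one who stops early there is no stated date. Staff would have to choose the date of the primary-outcome swab case by case, in one arm only.

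At stake are an estimate pulled toward the null, or past it if there is no true effect, and some loss of power in a design with little to spare. A diluted estimate would also enter the futility assessment in Section 13, which recalculates the required sample size from interim data and compares it with 420.

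**Working it through.** **Step 1. Inputs.** From Section 2.3: control risk 20.5%, a 50% reduction (hence 10.25%), 80% power, effective N 372, 378 after the ICC, 420 after 10% loss. From Section 13: alpha 0.05, two-sided. From Section 3.5: 1:1 allocation. Not in the documents, so assumed: the lag *d* in weeks between the two arms' ends of intervention.

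**Step 2. The plan's own figure.**
- Poisson regression, binary 1:1 predictor, null variance at the base rate: N = [1.96·√(2/(0.5·0.205)) + 0.8416·√(1/(0.5·0.205) + 1/(0.5·0.1025))]² / (ln 0.5)² = 364.
- Unpooled two-proportion formula: per arm (1.96 + 0.8416)²·(0.205·0.795 + 0.1025·0.8975)/0.1025² = 191, total 382.
- Both are within 3% of 372, and 378/0.90 = 420. The figure reproduces, with one common follow-up length in both arms.

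**Step 3. Effect of a lag.** Assume a constant hazard, a 12-month year of 52.18 weeks, and that every infection since baseline is counted.
- E-WORTH risk with the planned effect: 1 − (1 − 0.1025)^((52.18 + d)/52.18).
- E-WORTH risk with no true effect: 1 − (1 − 0.205)^((52.18 + d)/52.18).
- Each is divided by 0.205 to give the observed risk ratio.
- Power (pooled two-proportion test, n = 186 per arm): Φ{[(p₁ − p₂) − 1.96·√(2p̄(1 − p̄)/n)] / √([p₁(1 − p₁) + p₂(1 − p₂)]/n)}.

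| Assumed lag (weeks) | Extra time at risk | E-WORTH risk, planned effect | Observed RR | Power | RR with no true effect |
|---|---|---|---|---|---|
| 0 | 0% | 10.25% | 0.50 | 78.5% | 1.00 |
| 1 | 1.9% | 10.4% | 0.51 | 76.8% | 1.02 |
| 4 | 7.7% | 11.0% | 0.54 | 71.3% | 1.07 |
| 8 | 15.3% | 11.7% | 0.57 | 63.5% | 1.13 |
| 12 | 23.0% | 12.5% | 0.61 | 55.3% | 1.20 |

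**Step 4. Why these are upper bounds.** If the only follow-up swab is at 12 months, an infection that was acquired and then treated or cleared is not seen, so extra weeks add less than in proportion. As a low-incidence illustration, let a detectable infection last D months on average (assumed). One extra month then multiplies the E-WORTH risk by (1 − e^(−13/D))/(1 − e^(−12/D)), which is 1.005, 1.02 and 1.05 for D = 3, 6 and 12. The planned 10.25% becomes 10.3%, 10.5% and 10.7%, and power about 78%, 76% and 74%. The four-week row above gives 71%.

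**The case against.** **The lag is not stated, and it could be short.** This stands. A reader might infer that E-WORTH must end at least several weeks after randomization, or that the 28-day rule imposes a wait. The documents support neither. Section 3.6 gives the number and length of sessions but no spacing, and the 28 days in Section 3.5 triggers individual delivery; it is no minimum delay. Separate visits are likely, because each session reviews the previous one and is paid separately, but their spacing is inference. At one week the loss is about 2 points of power.

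**The bias is conservative.** Also true: it cannot manufacture an apparent benefit of E-WORTH. It still distorts the estimate, and the test is two-sided, so with no true effect it leans toward apparent harm. Its reach through the futility rule is limited, because that rule needs every primary outcome, behavioral ones included, to exceed 420 and leads first to discussion with the funder.

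**End-of-intervention timing has a purpose.** It gives both arms the same time since their programme ended, and Section 13 does value sustained impact. But the outcome is defined as infection accumulated since baseline, and for that equal time from randomization is what matters.

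**Re-anchoring has a cost.** If the lag were long, a 3-month visit counted from randomization would fall close to the last session. This stands for the 3-month visit. It has little force at 12 months, where the primary STI outcome is measured.

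**Conclusion.** The point holds in direction and rests on the text: E-WORTH women have a longer interval from baseline swab to 12-month swab, the visit date is undefined for those who do not finish, and no adjustment is described. The primary STI comparison is biased against E-WORTH.

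The size cannot be fixed from the documents. Over an assumed 1 to 12 weeks the planned risk ratio of 0.50 would appear as about 0.51 to 0.61, and power would fall from 78.5% to between 77% and 55%. These figures rest on a constant hazard, the planned rates, 186 women per arm analyzed, and every infection since baseline being counted. The last assumption makes them upper bounds. A reader might take 55% as the expected power; that needs a 12-week lag, which nothing in the documents establishes. The missing date for non-completers is a defect whatever the lag.

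**What to change.** 1. Define the 12-month primary-outcome visit and its window from the date of randomization in both arms, and say that this applies to women who miss sessions or never finish.
2. Preferably define the 3- and 6-month visits the same way, and replace the end-of-intervention wording wherever it sets a visit date.
3. State the session spacing and planned length of E-WORTH, so that the lag is known.
4. If any visit stays anchored to the end of the intervention, give a date rule for non-completers. Include the time from baseline swab to follow-up swab in the primary STI model, for example a complementary log-log or Poisson model with a log-time offset, or report such a model as a sensitivity analysis. With a single follow-up swab the offset can over-correct, for the reason in Step 4, so the common anchor is the better remedy.

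The cost is protocol wording and visit scheduling. The downside is that the E-WORTH 3-month visit falls sooner after the last session, and this grows with the lag.
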